## Abstract

**Introduction:** Bipolar disorder (BD) is a prevalent and disabling mental disorder characterized by disrupted circadian rhythms and impaired neurocognitive features, both of which fall under the major domains of Research Domain Criteria (RDoC). However, there is limited evidence regarding the interaction between circadian rhythms and long-term neurocognitive functioning. Therefore, this longitudinal cohort study protocol aims to explore whether circadian rhythm can predict changes in neurocognitive functioning over time in patients with BD.

**Methods:** This study adopts a longitudinal cohort design, aiming to recruit 100 BD patients in either depressive or remitted states. Participants will undergo evaluations from clinical, circadian rhythm, and neurocognitive perspectives at baseline, 6-month, and 12-month follow-ups, involving questionnaires, actigraphy, and computed neurocognitive tests. We will examine both cross-sectional and longitudinal associations between participants’ circadian rhythm patterns and neurocognitive functioning. Statistical analyses will employ Spearman correlation and mixed regression models.

**Discussion:** We anticipate that circadian rhythms may serve as predictors of neurocognitive functioning changes. The findings of this study could offer supplementary insights into BD pathophysiology, potential treatment targets, and prediction.

**Trial Registration:** This study has been registered with the Chinese Clinical Trial Registry under the registration code ChiCTR2200064922 on 21st October 2022.

## Introduction

Bipolar disorder (BD) is characterized by alternating manic/hypomanic episodes and depressive episodes, with an incidence of about 1% − 4% and suicide mortality 20-30 times higher than that in the general population [1,2]. As a significant biological feature, disrupted circadian rhythms have been highlighted by the International Society for Bipolar Disorders (ISBD). Among BD patients, delayed and disrupted chronotypes, changes in circadian rhythm gene expression, and abnormalities in cortisol and melatonin levels are commonly observed, showing correlations with prognosis, social functioning, and lithium response [3–6]. Considering that many studies have utilized subjective measurements, such as rhythm questionnaires and sleep diaries, objective measurements appear more reliable, including actigraphy, polysomnography, and the concentration of correlated hormones, especially melatonin and cortisol in serum, saliva, hair, and urine [7]. However, despite actigraphy being highly recommended for circadian rhythm evaluation, its limited application in long-term BD studies due to a scarcity of prospective designs has been noted [8].

Moreover, neurocognitive impairment, a distinctive feature of BD, has garnered significant attention due to its impact on the quality of life and long-term rehabilitation, contributing to BD being ranked as the second greatest cause of days out of role [1,9]. Commonly affected cognitive domains in BD encompass working memory, sustained attention, and executive functions [10]. While Lancet reviews have almost universally suggested that BD patients exhibit neuroprogressive characteristics resembling schizophrenia, previous longitudinal studies have yielded uncertain conclusions, highlighting the heterogeneity of cognitive phenotypes [1,2]. As BD staging and phenotyping of rhythmic and cognitive states gain popularity, the Research Domain Criteria (RDoC) has separately incorporated constructs related to circadian rhythms, attention, and working memory into arousal and regulatory systems, as well as cognitive systems, encouraging investigations into neurocircuitry and advancing future disorder classifications [11,12].

Interestingly, exploring circadian rhythm influence on neurocognitive functioning seems feasible with potential pathophysiological inspirations [13]. Recent studies focusing on Alzheimer’s and other neurodegenerative diseases have speculated on the involvement of seasonal cognitive plasticity and circadian rhythm disruption in neurocognitive functioning changes [14–17]. Additionally, a few pieces of evidence also support such an association with mental disorders [18]. For instance, rats subjected to chronic jet lag simulation demonstrated enhanced depressive behaviors and cognitive deficits [19]. Large-scale UK Biobank data revealed an association between disrupted circadian rhythmicity in mood disorders and cognitive function [20]. Moreover, the ‘desynchronization effect’ resulting from evening chronotypes and circadian disruption might render individuals vulnerable to cognitive and psychiatric challenges [21]. Furthermore, certain molecules are believed to play a role in both circadian rhythm disruption and neurocognitive impairment, mediated through mechanisms like immune-inflammatory activities [22,23].

Regrettably, up to this point, no study has been found that focuses on the long-term clinical correlation between circadian rhythm and neurocognitive functioning in BD patients. Exploring such a correlation holds utmost importance because, if the speculation proves true, 1) it could aid in identifying patients with a worse cognitive prognosis through circadian rhythm evaluation, enabling early intervention when necessary; 2) it may open up new possibilities for treating neurocognitive impairment in BD, for example, from a rhythmic perspective, such as brain synchronization; 3) it would provide stronger evidence supporting the pivotal role of circadian rhythm in BD pathophysiology [24].

Therefore, this study protocol was designed to bridge the current research gaps by investigating the predictability of neurocognitive functioning through circadian rhythm in BD. The objective of this study is to assess whether circadian rhythm could predict the long-term change in neurocognitive functioning among BD patients. It is hypothesized that circadian rhythm could predict the long-term change in neurocognitive functioning.

## Methods and analysis

### Setting and recruitment

This study follows a longitudinal cohort design, as depicted in Figure 1, with participant evaluations scheduled at baseline, 6-month follow-up, and 12-month follow-up after recruitment. Participants who miss the 6-month follow-up will still be eligible for the 12-month follow-up assessment. Ethical approval was obtained from the Research Ethics Committee of the First Affiliated Hospital of Chongqing Medical University (Approval Number: 20227001). Furthermore, this study has been registered with the Chinese Clinical Trial Registry under the registration code ChiCTR2200064922 on 21 October 2022. The study will be conducted in accordance with the Declaration of Helsinki [25].

**Figure 1. F0001:**
[figure not shown]
Flow diagram illustrating the procedures for participant enrollment and assessment.

Recruitment will be conducted at the Psychiatric Outpatient Department of The First Affiliated Hospital of Chongqing Medical University in China, which is one of the largest hospitals with an esteemed reputation in southwest China. Recruitment advertisements will be disseminated online, providing contact information for interested patients. Additionally, researchers will proactively contact potential participants based on electronic medical records and expert referrals. Participants will not receive any economic compensation, except for assistance with making outpatient appointments. The recruitment period will span from January 2023 to July 2023. Participants will have the autonomy to withdraw from the study, with reasons and dates recorded. No specific replacement plan is in place for participants who choose to drop out.

The inclusion criteria are as follows: 1) aged 18–45 years old, either female or male; 2) diagnosed with bipolar disorder according to the Diagnostic and Statistical Manual of Mental Disorders-5 (DSM-5), which will be confirmed by researchers using Structured clinical interview for DSM-5, research version (SCID-5-RV) [26,27]; 3) currently in depressive or remitted states, as indicated by a YRMS score < 6; 4) eligible to complete the required examinations; 5) signed written informed consent to participate in this study.

The exclusion criteria are as follows: 1) presence of other diseases that could severely impact circadian rhythm or neurocognitive functioning, such as amnesia, stroke, sleep apnea, obesity, hyperthyroidism, diabetes, brain injury, and cortisol or melatonin related endocrinopathy; 2) living conditions that might influence circadian rhythm or neurocognitive functioning, including engaging in shift work more than once a week, residing across time zones with a time difference exceeding two hours and a shifting frequency of more than once a month, and being in the perinatal or lactation period; 3) concurrent severe psychoactive substance use, defined as consuming alcohol more than twice a week, smoking over 20 cigarettes a day, or using psychedelics or other illegal substances; 4) currently experiencing strong suicidal ideation or attempt, or exhibiting high-risk impulsive, violent, or self-injurious behaviors necessitating immediate hospitalization or constant supervision; 5) having undergone electroconvulsive therapy within the last 6 months prior to recruitment.

The participants should not receive electroconvulsive therapy during the study; otherwise, their follow-up will be terminated. No other specific treatment requirements are in place.

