### Statistical analysis

SPSS (version 26) will be used for the analysis of this study. Histograms will be used to determine the normality or approximate normality of the data. This will be achieved by combining them with the Shapiro-Wilk test [60]. Descriptive analyses will be performed to examine participant and disease characteristics, as well as data from clinical, circadian rhythm, and neurocognitive functioning assessments. Missing value analyses will be conducted with multiple imputation or expectation maximization methods to handle any missing data.

Spearman correlations will be employed to compare subjective and objectively assessed circadian rhythm patterns. Subjective assessments include MEQ, SPAQ, and PSQI results, while objective assessments will primarily rely on behavioral data.

Longitudinal analyses will involve calculating changes in SAS, SDS, HAMD, HAMA, and YMRS scores, and correlating these difference scores (baseline minus 6-month follow-up, baseline minus 12-month follow-up) with circadian rhythm parameters for each participant using Spearman correlation. Mixed regression models will be used to determine if changes in circadian rhythm significantly predict changes in neurocognitive functioning from baseline to 6-month follow-up and 12-month follow-up [61]. Stepwise adjustment of covariates will be employed to construct several regression models to explore the robustness of the relationship between circadian rhythm and neurocognitive functioning. Adjustments will be made for other factors that may influence these associations, such as disease duration, age, gender, current medication use, education level, and severity of emotional symptoms.

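### Ending follow-up after on-study electroconvulsive therapy (ECT) leaves scheduled cognitive outcomes uncollected because of a post-baseline clinical event; continuing the visits is cheap, and the bias is probably small unless ECT is common.

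*Protocol article*

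**What the plan says.** All but the last of these statements stand in the protocol article under Setting and recruitment.

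- On-study rule, after the exclusion criteria: "The participants should not receive electroconvulsive therapy during the study; otherwise, their follow-up will be terminated". It has no time limit, no route back and no stated reason.
- The next sentence: "No other specific treatment requirements are in place".
- Exclusion criterion 5 bars patients "having undergone electroconvulsive therapy within the last 6 months prior to recruitment". A patient whose last ECT was earlier than that may enter and contribute cognitive data.
- Visits: "participant evaluations scheduled at baseline, 6-month follow-up, and 12-month follow-up after recruitment". On a missed visit: "Participants who miss the 6-month follow-up will still be eligible for the 12-month follow-up assessment".
- Statistical analysis section: "Missing value analyses will be conducted with multiple imputation or expectation maximization methods to handle any missing data". As published, it does not treat ECT terminations separately.

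**The concern.** The objective is to learn whether circadian rhythm predicts cognitive change over 12 months, and the primary outcome is a cognitive composite. In a cohort that assigns no treatment, ECT is something that happens in the course under study. Ending observation when it happens ties the missing outcomes to that course.

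Two features make the clause hard to defend as it stands. The plan tolerates ECT more than 6 months before a cognitive assessment at entry, but not on study. It also tolerates a gap at the middle visit, but not if ECT is the reason.

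At stake are outcome data that no later analysis plan can recover, in a study that already expects 50% dropout without replacement.

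**Working it through.** **1. The rules side by side.** Suppose a participant's ECT ends at month t of follow-up. At the 12-month visit the gap is 12 − t months. It is at least 6 months when t ≤ 6, about the gap accepted at entry. For t > 6 the 12-month visit falls inside 6 months of ECT. So the comparison with the entry window helps only for ECT finished by about month 6. If ECT timing were uniform over the year (assumption), that is 6/12, or half, of those who receive it.

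**2. The plan's own sample size.** Inputs from the Sample size calculation section: difference 13, SD 21, alpha 0.05, power 0.80. I take the test as two-sided.

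- n = 2 × (21 × (1.960 + 0.842) / 13)² = 40.96, so 41, as stated. The exact t calculation gives 41.9, so 42.
- 41 / (1 − 0.5) = 82, against 81 stated. The difference is immaterial, and 100 are planned.
- The ECT clause does not enter this calculation.

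**3. Numbers lost.** No ECT rate is given, so I assume p = 2%, 5%, 10% or 15% of 100 patients. I take the loss as additional to the 50% dropout, which is the harsher case. Completers = 100 × (1 − p) × 0.5.

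| Assumed ECT rate | Terminated | Completers | At least 6 months past ECT at month 12 (uniform timing) |
|---|---|---|---|
| 2% | 2 | 49 | 1 |
| 5% | 5 | 47.5 | 2.5 |
| 10% | 10 | 45 | 5 |
| 15% | 15 | 42.5 | 7.5 |

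Completers fall below 41 only when p exceeds 1 − 41/50 = 18%. Here 41 serves only as the plan's own count; it was not derived for the rhythm-cognition slope.

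**4. Possible bias, first model.** Assume a standardised slope of 0.30 of cognitive worsening on rhythm disruption. ECT propensity has correlation w with cognitive worsening, and the top fraction p is removed (2,000,000 draws, no imputation).

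| ECT rate | w = 0 | w = 0.3 | w = 0.6 |
|---|---|---|---|
| 2% | 0.301 | 0.298 | 0.291 |
| 5% | 0.301 | 0.296 | 0.282 |
| 10% | 0.301 | 0.294 | 0.272 |
| 15% | 0.301 | 0.292 | 0.264 |

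At w = 0 there is no bias; 0.301 is simulation noise. At w = 0.3 the slope is 0.5% to 3% too small, and at w = 0.6 it is 3% to 12% too small. At w = 0.6, mean change among those kept looks 0.03 to 0.16 SD too favourable.

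**5. Possible bias, second model.** Let relapse severity be R = 0.4X + error, with X the rhythm disruption, and cognitive change Y = −0.15X − 0.4R + 0.8 × error. The slope of Y on X is −0.15 − 0.4 × 0.4 = −0.31.

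- Removing exactly the most severe 2%, 5% or 10% on R shrinks the slope by about 5%, 9% or 13%.
- If ECT propensity correlates only 0.5 with R, the shrinkage is about 1%, 2% or 3%.
- If R is adjusted for, the slope on X is −0.15 before and after removal, so there is no bias.
- With 50 completers the standard error of the slope is about 0.13. The largest shift above is 0.13 × 0.31 = 0.04.

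**6. Omitting only the assessments within 6 months of ECT.** In the second model with noise-free removal and uniform timing, about half of the ECT patients are still missing at month 12. The remaining shrinkage is about 2%, 4% or 6%, so this restriction should not be the only analysis.

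Neither model includes an effect of ECT itself on the scores. If ECT propensity rose with rhythm disruption but fell with cognitive worsening, the slope could shift the other way.

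**The case against.** The strongest case against runs as follows.

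- **The two ECT rules do not contradict each other.** A reader might infer that the termination clause conflicts with the 6-month window. It does not: the window is an entry criterion, the clause covers the study period, and both can be applied. ECT before entry lies outside the change being measured, and ECT during follow-up lies inside it. This stands. What remains is an uneven standard with no stated reason.
- **Who receives ECT is unknown.** A reader might infer that the clause removes the patients with the worst course. The documents do not say who would receive ECT, how often or why. Entry already excludes patients "exhibiting high-risk impulsive, violent, or self-injurious behaviors necessitating immediate hospitalization or constant supervision", among other high-risk groups. This stands. A link with illness course is plausible, not documented, and a worse mood course need not mean worse cognitive change.
- **The plan may already absorb part of the loss.** Models will be adjusted for severity of emotional symptoms. A participant with ECT after month 6 can already have 6-month mood, actigraphy and cognitive data for imputation to use. This stands in part. With visits 6 months apart, a deterioration that leads to ECT between them may never be recorded.
- **Post-ECT scores may reflect ECT.** This is a good reason to analyse such assessments separately. It is not a reason to leave them uncollected.
- **The study calls itself exploratory.** That limits the weight of the point but does not remove it.

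**Conclusion.** The point holds in a limited form. The protocol leaves scheduled outcome assessments uncollected because of a post-baseline clinical event. Its missing-data methods correct for this only if observed data explain the loss. Delta-adjusted sensitivity analyses could explore the uncertainty but could not recover the data.

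Size and direction cannot be derived, because the documents give no ECT rate, timing or link with cognition. A reader might infer that the rhythm-cognition slope is biased toward zero by 5% to 13%. The documents do not support that: those figures need ECT to remove exactly the most severe patients and need severity to be left out of the model. Under weaker links the shift is a few percent or nothing, well inside the sampling error for about 50 completers. The bias is probably small unless ECT is common. The plan's 41 completers are safe at every assumed rate up to 15%.

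The case for change rests on an avoidable, irreversible loss against a very low cost, not on a demonstrated large bias.

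**What to change.** Replace the consequence in the termination clause with wording such as:

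> *Participants who receive ECT during the study will, if they consent, continue with the scheduled 6- and 12-month assessments. Dates of ECT will be recorded. ECT will be treated as an intercurrent event. The association between rhythm and cognition will be reported with all observed assessments, and again without post-ECT assessments (for example, those within 6 months of the last ECT).*

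If there is a reason to treat on-study ECT differently from ECT more than 6 months before entry, state it next to the clause.

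The cost is a small wording change and a few visits that are already in the schedule (Table 1). The downside is that a few post-ECT assessments, which may reflect ECT itself, must be flagged and analysed both ways. The change concerns data collection only and takes no view on whether ECT is given.

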### Assessment

Schedule of the enrolment and assessment was listed in Table 1.

**Table 1. t0001:** Schedule of enrolment and assessment.

Time point		Study periods		
		Baseline	6-month follow-up	12-month follow-up
Enrolment	Eligibility screen, informed consent, assessments	×		
Clinical assessment	HAMD-17, HAMA-14, YMRS, CGI-BP, SAS, SDS	×	×	×
Circadian rhythm assessment	MEQ, SPAQ	×		
	Actigraphy, PSQI	×	×	×
Neurocognitive assessment	DMS, PAL, RVP and SWM tests in CANTAB	×	×	×

Note: SAS: Zung’s self-rating anxiety scale; SDS: Zung’s self-rating depression scale; HAMD-17 : 17-item hamilton depression scale; HAMA-14:14-item hamilton anxiety scale; YMRS: young mania rating scale; CGI-BP: clinical global impressions-bipolar version; MEQ: morningness eveningness questionnaire; SPAQ: seasonal pattern assessment questionnaire; PSQI: Pittsburgh sleep quality index; DMS: delayed matching to sample; PAL: paired associates learning; RVP: rapid visual information processing; SWM: spatial working memory; CANTAB: Cambridge neuropsychological test automated battery.

#### Clinical assessment

Sociodemographic variables will be collected at baseline, including age, sex, height, weight, body mass index (BMI), ethnicity, education level, family history of mental illness, economic situation, handedness, history of tobacco and alcohol use and marriage status. We will also record the duration of illness, age of onset, subtypes of bipolar disorder, history of suicidal ideation and attempt, and history of psychotic symptoms.

For mood symptom monitoring at baseline, 6-month follow-up and 12-month follow-up, we will use the 17-item Hamilton Depression Scale (HAMD-17) and 14-item Hamilton Anxiety Scale (HAMA-14) which are interviewer-rating scales for depression and anxiety; Zung’s Self-Rating Depression Scale (SDS) and Zung’s Self-Rating Anxiety Scale (SAS) which are self-rating scales for depression and anxiety; and Young Mania Rating Scale (YMRS) which is an interviewer-rating scale for mania [28–33].

Other evaluation includes the Clinical Global Impressions-Bipolar Version (CGI-BP). CGI-BP is an interviewer-rating scale for disease severity and treatment efficacy [34].

#### Circadian rhythm assessment

The circadian rhythm variable consists of two components: subjective questionnaires and objective behavioral data. The questionnaires used include the Morningness Eveningness Questionnaire (MEQ), the Pittsburgh Sleep Quality Index (PSQI), and the Seasonal Pattern Assessment Questionnaire (SPAQ). The MEQ is a 19-item self-rating scale used to evaluate chronotype, with scores indicating evening, intermediate, or morning types [35]. The PSQI is an 18-item self-rating scale that assesses sleep quality and disturbances, and a validated Chinese version will be used [36,37]. The SPAQ is a widely used questionnaire for evaluating seasonal effects on mood and behavior. It includes a general seasonality score (GSS) that can be used to screen for seasonal affective disorder (SAD) [38,39]. Except for the SPAQ, all the aforementioned scales and questionnaires have already been validated or translated into Chinese versions.

On the day of evaluation, participants will be asked to wear a wrist-worn actigraph device (wGT3X-BT, v1.9.2, ActiGraph LLC) for 14 consecutive days and nights. The actigraph’s flashing light will be disabled throughout the monitoring period. The device will continuously record physical activity, sleep/wake information and sedentary time using a sampling frequency of 100 Hz. Participants will be instructed to continuously wear the actigraph except during activities such as showering, swimming, or any activity that would consistently expose the device to water for more than 30 min. Data retrieval and analyses will be performed using the ActiLife software program (version 6.13.4) with 60-second epochs [40]. The collected raw data will be stored and analyzed using publicly available algorithms. Non-wear time will be defined as 60 consecutive minutes of zeros with a 2-minute spike tolerance based on the default Wear Time Validation algorithm provided by Actilife 6.13.4. Any non-wearing epochs will be excluded from the analysis without any data imputation [41,42]. For a day to be deemed valid, it must have a minimum of 20 h of wearing time [42]. A participant will be considered valid if they have a minimum of 7 valid days, including at least 5 weekdays and 2 weekend days [35].

The circadian rhythms of sleep-wake activity will be calculated using Cole-Kripke Algorithm in Actilife [43,44]. We will retrieve sleep parameters such as Sleep Onset (SO), Total Sleep Time (TST), Wake after Sleep Onset (WASO) and Sleep Efficiency (SE). SO means the first minute that the algorithm scores ‘asleep’. TST equals to the total number of minutes scored as ‘asleep’. WASO means the total number of minutes the subject was awake after SO occurred. SE represents the number of sleep minutes divided by the total number of minutes the subject was in bed (i.e. the difference between the In-Bed and Out Bed time) [44].

The circadian rhythm parameters of physical activity will be calculated using the specialized GGIR package for R software [45]. Non-parametric circadian rhythm analysis will be employed. We aim to determine the intradaily variability (IV), interdaily stability (IS) and relative amplitude (RA) of the rest-activity rhythms [43,46,47]. IV refers to the consolidation of rest-activity states within a day, where higher values indicate greater fragmentation of the rhythm with more transitions between rest and active states [45]. IS describes the consistency of rest-activity patterns across different days, with higher values indicating greater stability [48]. RA represents the difference in activity between the most active 10-hour period (M10) and the least active 5-hour period (L5) and serves as a marker of amplitude strength [46]. Time of sedentary and moderate-to-vigorous physical activities (MVPA) will also be calculated based on validated activity cut-points in Actilife [35,49,50].

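### The 60-minute-zeros non-wear rule has no sleep exemption, so long still runs of worn sleep are deleted and can cost valid days

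*Protocol article*

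**What the plan says.** All of the rules are in the protocol article, under Circadian rhythm assessment.

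- **Wear schedule:** the wrist device is worn "for 14 consecutive days and nights".
- **Processing:** "ActiLife software program (version 6.13.4) with 60-second epochs".
- **Non-wear:** "Non-wear time will be defined as 60 consecutive minutes of zeros with a 2-minute spike tolerance", following the ActiLife default.
- **Handling:** "Any non-wearing epochs will be excluded from the analysis without any data imputation".
- **Valid day:** "For a day to be deemed valid, it must have a minimum of 20 h of wearing time". A valid participant needs at least 7 such days, of which 5 or more are weekdays and 2 or more are weekend days.
- **Sleep measures:** total sleep time (TST) is the count of minutes scored asleep, and sleep efficiency (SE) divides sleep minutes by minutes in bed. Both come from the Cole-Kripke algorithm in ActiLife.
- **Rhythm measures:** IV, IS and RA are computed in the GGIR package for R. The text glosses RA thus: "RA represents the difference in activity between the most active 10-hour period (M10) and the least active 5-hour period (L5").

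The Discussion confirms that no sleep diary is used. The Statistical analysis section makes change in circadian rhythm the predictor of change in neurocognitive functioning.

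**The concern.** A rule that reads an hour of zeros as an absent device is safe only if a worn device rarely gives an hour of zeros. Sleep is where that is least secure, and this device is worn through every night. The section sets no exception for the night or for time in bed, and without a diary no participant record separates still sleep from removal.

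The deleted minutes are ones that ought to count as sleep. The error is also not random across people, because the more motionless the sleeper, the more is removed. Participants may be depressed or remitted, and treatment is unrestricted apart from electroconvulsive therapy. Stillness at night may therefore change between visits, and any such change would pass into the change scores used as predictors. Adjusting for medication and symptom severity does not bring deleted epochs back.

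The 20 h threshold adds a second route. Enough flagged sleep invalidates the whole day, and enough lost days remove the participant's actigraphy.

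**Working it through.** The plan gives no figure for this point, so there is none to reproduce. The check applies the stated rules to assumed nights.

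**Inputs from the protocol article:** 60-second epochs; 60 zero minutes with a 2-minute spike tolerance; deletion without imputation; 20 h of wear per valid day; at least 5 valid weekdays and 2 valid weekend days out of 14 days.

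**Assumed inputs, not in the documents:** a night of 480 minutes in bed with 420 asleep; how often the wrist is still for an hour; illustrative M10 and L5 levels.

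**1. Valid day.** The allowance is 24 h − 20 h = 4 h = 240 minutes, shared with genuine removals. With 240 flagged minutes, wear is 20 h and the day stands. With 300, wear is 19 h and the day is lost.

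**2. TST and SE, if the mask is applied before sleep scoring.** With f flagged sleep minutes, TST = 420 − f. SE is (420 − f)/480 if time in bed is left alone, or (420 − f)/(480 − f) if it is cut too.

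| f (min) | TST (min) | SE, in-bed time kept | SE, in-bed time cut |
|---|---|---|---|
| 0 | 420 | 87.5% | 87.5% |
| 60 | 360 | 75.0% | 85.7% |
| 120 | 300 | 62.5% | 83.3% |

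At f = 60 the loss of TST is 60/420 = 14%. The effect on SE depends heavily on a handling choice that the text does not state.

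**3. How much might be flagged.** The rule was run on simulated worn 480-minute nights, with movement bouts of 1 to 6 minutes separated by still gaps of varying mean length. The spike tolerance was read in two ways: up to 2 consecutive non-zero minutes, or up to 2 non-zero minutes in the 60-minute window.

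| Mean still gap (min) | Mean flagged minutes (consecutive / total reading) | Days below 20 h (consecutive / total reading) |
|---|---|---|
| 15 | 102 / 79 | 6% / 2% |
| 30 | 261 / 253 | 62% / 56% |
| 45 | 331 / 333 | 89% / 89% |
| 60 | 379 / 384 | 96% / 96% |

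If non-zero minutes are instead scattered singly at random over 20% of the night, the two readings flag 427 minutes and about 1 minute. The result runs from almost nothing to almost the whole night, depending on wrist stillness and on how the tolerance works.

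**4. Valid participant.** Take 10 weekdays and 4 weekend days, with each day lost independently with probability q. The chance of meeting the criterion is P(at least 5 of 10) × P(at least 2 of 4). This is about 0.87 at q = 30%, 0.68 at 40% and 0.43 at 50%.

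**5. L5 and RA, only if the ActiLife mask is carried into GGIR.** Deleting z zero minutes from a fixed 300-minute L5 window multiplies its mean by 300/(300 − z): 1.11 at 30 minutes, 1.25 at 60 and 1.67 at 120. Take an illustrative M10 of 40 and L5 of 4, so RA = (40 − 4)/(40 + 4) = 0.82. With 60 minutes deleted, L5 = 5 and RA = 35/45 = 0.78. With 120 deleted, L5 = 6.67 and RA = 33.33/46.67 = 0.71. A large percentage change in L5 is a smaller one in RA.

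**The case against.** The strongest reply has four parts.

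- **The size is assumed.** The frequency of hour-long zero runs in sleep is not in the documents, and the check shows how wide the range is. This stands. It limits what can be said about magnitude, but not the reading of the rule.
- **The rule belongs to ActiLife, while IV, IS and RA come from GGIR.** Nothing says that the mask passes from one to the other. This stands too. A reader might infer that L5 is inflated by 11% to 67% over 30 to 120 deleted minutes, but that depends on a link the text does not state. L5 is also not listed as a parameter in its own right.
- **Exclusion without imputation and the 20 h day are deliberate choices with cited sources.** This is fair. Filling gaps from the same clock time on other days would be a preference, not a correction. It does not answer the point, however, because the trouble lies in what is classed as non-wear.
- **The authors call the study exploratory, and the sample size does not rest on these measures.** This lowers the stakes, but the actigraphy measures are still part of the exposure.

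A further inference is tempting from the RA sentence: that the study will analyse the plain difference M10 − L5, which mixes rhythm strength with overall activity. The text does not establish this. The sentence is a one-line gloss on a named index, computed by a named package under a cited method. It omits the denominator and should be corrected as wording, but no distorted exposure follows from it.

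**Conclusion.** The point holds for the non-wear rule. Followed as written, it deletes worn sleep with zero counts for about 60 minutes or more. It can lower ActiLife TST, alter SE, and invalidate any day with more than 240 flagged minutes, with the largest losses in the stillest sleepers. The effect on TST and SE assumes that flagged epochs are removed before sleep is scored. The text supports this by excluding them from the analysis without limitation, but it does not spell out the order.

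The size is unknown. The 14% loss of TST and the simulated ranges are illustrations under assumed nights, not estimates for this cohort. Any effect on L5 and RA is conditional on the mask being carried into GGIR.

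A reader might go further and infer that the rule reverses the ordering of participants on the exposure. The deletions do fall unevenly, but nothing in the documents or the check shows ranks changing, so that claim should not be made.

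**What to change.** 1. State that a zero run inside the detected sleep or in-bed window does not count as non-wear, either for epoch exclusion or for the 20 h rule, unless it is contiguous with a daytime non-wear bout. Alternatively, use GGIR's raw-acceleration non-wear detection on the stored 100 Hz data.
2. State which non-wear mask applies to IV, IS and RA.
3. Run one sensitivity analysis under the rule as now written, and report valid days and participants under both.
4. As a wording correction only, print RA = (M10 − L5)/(M10 + L5).

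The cost is a change to the processing script and a few sentences of text. No new data are needed, because the raw recordings are kept and GGIR is already in use for the rhythm parameters. The small downside is that some true overnight removals may be kept as sleep, and the sensitivity analysis shows how far that matters.
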